## Abstract

Background: There is a risk of pelvic floor dysfunction (PFD) from baby delivery. Many clinical guidelines recommend pelvic floor muscle training (PFMT) as the conservative treatment for PFD because pelvic floor muscles (PFMs) play a crucial role in development of PFD. However, there is disagreement about the method and intensity of PFM training and the relevant measurements. To pilot the study in PFM training, we designed a Pelvic Floor Workout (PEFLOW) for women to train their pelvic through entire body exercises, and we planned a trial to evaluate its effectiveness through comparing the outcomes from a group of postpartum women who perform PELFLOW at home under professional guidance online with the control group. Methods/design: The randomized controlled trial was projected to be conducted from November 2021 to March 2023. A total of 260 postpartum women would be recruited from the obstetrics departments of the study hospital and women would be eligible for participation randomized into experimental or control groups (EG/CG) if their PFM strength are scaled by less than Modified Oxford grading Scale (MOS) to be less than grade 3. Women in EG would perform a 12-week PEFLOW online under the supervision and guidance of a physiotherapist, while women in CG would have no interventions. Assessments would be conducted at enrollment, post intervention (for EG) or 18th to 24th week postpartum (for CG), and 1 year postpartum. Assessment would be performed in terms of pelvic floor symptoms, including MOS, cough stress test, urinary leakage symptoms, pelvic organ prolapse quantitation (POP-Q), and vaginal relaxation, clinic examinations including Pelvic floor electrophysiological test, Pelvic floor ultrasound and Spine X-ray, overall body test including trunk endurance test, handgrip test, body composition test, and questionnaires including International Physical Activity Questionnaire Score-Short Form(IPAQ-SF), Pelvic Floor Distress Inventory Questionnaire-20 (PFDI-20), Pelvic Floor Impact Questionnaire-7 (PFIQ-7), the 6-item Female Sexual Function Index (FSFI-6), and the Pittsburgh Sleep Quality Index (PSQI). Primary analysis will be performed to test our main hypothesis that PEFLOW is effective with respect to strengthen PFM strength. Discussion: This trial will demonstrate that pelvic floor-care is accessible to most women and clinical practice on PFD may change relevantly should this study find that Online PEFLOW approach is effective to improve PFMs. Trial registration: ClinicalTrials.gov, NCT05218239.

## 1. Introduction/Background

Pelvic floor dysfunction (PFD) is a series of symptoms of dysfunction caused by injuries on pelvic floor muscle, nerve, ligament, and fascia injury. PFD has a serious negative impact on the common life of woman, who would experience different degrees of urinary incontinence, pelvic organ prolapse, chronic pelvic pain, sexual dysfunction, etc. Although not clinically emergent, PFD brings a heavy economic burden to the women who suffers from this problem. The latest updated data show that the prevalence of urinary incontinence in Chinese women reaches 30.9%, the incidence of symptomatic pelvic organ prolapse is up to 9.6% [1], and the prevalence of sexual dysfunction is about 29.7% [2]. Pelvic floor diseases are more prevalent among women who have multiple births.

Pregnancy and vaginal delivery have independently been proved to be the risk factors for the development of severe urinary incontinent (SUI) as they could obviously weaken the pelvic floor muscle (PFM) strength. However, it was hard to evaluate patients’ muscle strength objectively; therefore, it was hard to validate whether a measure could be effective to have the weakened pelvic floor muscles be recovered before Modified Oxford scale (MOS) for muscle strength was published [3]. MOS provides quantitative scales for muscle strength, and it is simple and easy to apply clinically. It is becoming widely accepted method for pelvic floor muscle strength assessment since it was published. Literately and clinically, MOS 4 and 5 is identified as having “good” or “strong” muscle contraction which represents a normal condition of the pelvic floor muscles; relevantly MOS ≤3 indicates a weak contraction or no contraction being felt [4]. Some studies suggested that pelvic floor muscle strength be correlated with the incidence of pelvic organ prolapse (POP). Thus, Pelvic Organ Prolapse Quantification (POP-Q) was developed for evaluation of the pelvic floor muscle [5]. Borello-France et al. [6] used POP-Q to evaluated women’s pelvic floor muscle in their studies and argued that women with stage II of prolapse were better than those with stage III or IV in elevating their pelvic floor, and also would be easier to get benefit from PFM training than those over stage III. Scientific evidence showed that 10–20% of patients who were not intervened for the clinically confirmed POP got progressed in term of POP-Q scoring in 2-year follow-up [7,8], so early prevention or treatment should have high priority. The incidence rate of POP is higher in middle aged and elderly women. PFM training is recommended to women postpartum for it reduces the incidence of PFD during 6–12 months postpartum [9] and should possibly reducing the incidence of diseases from muscle dysfunction related to the anatomical changes with aging [10]. A program of supervised PFM training was recommended as a first option for women with symptomatic POP-Q stage I or stage II [11]. MOS and POP-Q can be the objective indicators be used to validate the effectiveness of any measure in improving PFM.

PFM training is the most popular conservative intervention for PFD. Its role in PFM improvement is becoming more and more important along with the rapid development of rehabilitation medicine and it is more and more acceptable by women as their requirements for improvement of quality of life are getting stronger. There are many kinds of programs for post-delivery exercises that are commercially available for women. Formulating a rehabilitation program after childbirth is certainly an effective strategy for most women to benefit from the post-delivery recovery. However, PFM rehabilitation relied on the synchronous recovery of both type I and type II muscle fibers, and, as it is difficult to identify type I and type II of the muscle fibers accurately by nonprofessionals during pelvic floor muscle contraction, exercises are usually not properly programmed, and the effectiveness of such programs are not easy to gain. Formulating a science-based rehabilitation program that can trained type I and type II muscle fibers for their synchronous rehabilitation after childbirth is certainly an effective strategy for most women to benefit from the post-delivery recovery.

Many pelvic floor rehabilitation methods were explored in previous studies. In 1948, Kegel training was first proposed and adopted as the gold standard of pelvic floor muscle training (PFMT) [12]. PFMT refers to the conscious exercise via autonomic contraction of the pelvic floor muscles that are dominated by pubococcinate muscles. The American Urogynecologic Society evaluated PFMT as the wisest exercise choice for women and recommended it as the first-line treatment for PFD [13]. Kegel exercise has rarely been used alone until now. The human body is an organic whole, so PFMT should not be limited to the local pelvic floor. In 1980, abdominal hypopressive technique (AHT) [14] was invented. It emphasizes PFMT to be combined with activation of transverse abdominis muscle and diaphragmatic breathing [14]. Some studies found that training of the core muscles, including rectus abdominis, transversus abdominis, internal or external oblique, lumbar multifidus, and erector spinae muscles [15] for their stability, such as Yoga exercises, can strengthen PFM [16,17]. A French therapist, Philippe, proposed a concept of Global Postural Re-education (GPR) [18,19] and demonstrated that GPR was advantageous in improving respiratory muscle strength and reducing urinary incontinence since GPR was projected to correct postural misalignments by stretching the muscle chains [19]. In consideration that the spine is a continuous boney structure that is closely associated with pelvic dynamics [20], some investigators in recent years focused their research on restoring the balance of anatomic mechanical systems through adjustment of the posture. It was found that therapeutic exercise on posture adjustment (diaphragm and lumbar position) for patients with poor respiration and posture can improve the neuromuscular control on muscles of deep abdomen, diaphragm, and pelvic floor, and promote the stability of lumbar and pelvic floor. In addition, a significant correlation between overall posture and PFD was also demonstrated in several studies [20,21].

In 2020, the Canadian Society of Obstetricians and Gynecologists (SOGC) recommended that, to gain effectiveness, PFMT should be performed under supervision for at least 3 months [22]. Some previous studies [23,24,25,26] in alleviation of symptomatic ureter leakage demonstrated that physical exercise with PFMT was effective on the pelvic floor muscle.

In referring to the above published studies and concepts and based on the previous study [27] of our team, our team from Peking University Peoples Hospital (PKUPH) developed a Pelvic Floor Workout (also named as PKUPH-PEFLOW), which focuses on training to improve the strength, endurance, flexibility, stability, and flexibility of core muscles, including diaphragmatic, abdominal, pelvic floor, and lower back muscles. We also designed a randomized controlled clinical trial to demonstrate the effectiveness of PEFLOW. The trial was designed on hypothesis that (1) a 12-week Global Pelvic Floor Workout would improve the pelvic floor muscle strength of postpartum women; (2) the 12-week Global Pelvic Floor Workout would positively impact on the overall function of postpartum women, including pelvic floor function, body posture, pain, etc.; and (3) body posture, physical activity level, trunk muscle endurance and strength would have beneficial effects on maternal overall function.

## 2. Methods

### 2.1. Study Design

This is a randomized controlled trial to be conducted from November 2021 to March 2023. Participants are recruited from the obstetrics departments of Peking University People’s Hospital. The study was approved by Peking University Institutional Review Board (number: 2021PHB254-001) and registered in Clinical.Trials.gov (number: NCT05218239). 

### 2.2. Inclusion Criteria

Postpartum women will be eligible for enrollment if they are: (1) in 6th to 12th week postpartum; (2) without history of clinically confirmed systematic diseases, such as neurological conditions and cardiac insufficiency, currently not wearing cardiac pacemaker or receiving hormone therapy, and/or not been treated with radical surgery for pelvis and sling or surgery for prolapse before pregnancy, and with no pregnant complications; (3) willing to participate signing informed consent form; and (4) able to read without cognitive problem from poor education or diagnosed mental problem.

### 2.3. Exclusion Criteria

Participants will be excluded if they are: (1) confirmed by postpartum pelvic examination to be >grade 3 of pelvic floor muscle strength by Modified Oxford Scale (MOS); (2) ≥stage III for Pelvic Organ Prolapse Quantification (POP-Q); (3) symptomatically confirmed to have severe urinary incontinence (Women with more than one incontinent episode per day AND an important volume of urine loss [28] or urine leakage occurred in a quiet state were classified as having severe urinary incontinence); or (4) any limb dysfunction that unenabled women to take this training. A participant will be recorded as“ drop off from trial” if she becomes pregnant during the follow-ups.

### 2.4. Site Investigators and Roles

To conduct and evaluate the project, the study should assign the following persons to play roles: (1) a gynecologist (can be the chief investigator) who would conduct baseline examination and evaluation for eligible women, and another two gynecologists who would conduct examinations at the second and third follow-up visits, respectively, who was unaware of the data from the last follow-up. The examinations would include MOS, POP-Q, cough stress test, and vaginal relaxation.

(2) A research coordinator who is responsible for informed consent, study record and data management, contacting with and be accompanied with the participants during the examinations.

(3) A physiotherapist who would apply the designed intervention to participant in experimental group (EG).

(4) A physiotherapist assistant who would be responsible for correcting actions of EG during training and record Borg’s Rating of Perceived Exertion 6-20 (RPE) Scale after each session of training. (5) Clinic examiners who would be responsible for pelvic floor surface electromyography (sEMG), pelvic floor ultrasound examination, and Spine X-ray. 

### 2.5. Randomization and Allocation Concealment

Eligible women would be randomized into two groups, the experimental group (EG) and the control group (CG), at a ratio of 1:1. A randomization list would be created by a statistician from Peking University for each center before the start of the research. Randomization would be performed using SAS 9.4 (SAS Institute, Cary, NC, USA). The randomization lists would be concealed until a woman is confirmed eligible for participation. Then, the research coordinator in the site would assign the eligible participant to EG or CG. With such a randomization, the numbers of participants in EG and CG are expected to be statistically balanced. Participants and the physiotherapists engaging in the intervention are not blind to the randomized assignment because it is not feasible to do. However, to minimize the risk of assessor’s unblinding, participants are blind to other’s assignments and encouraged not to discuss their treatment with the independent assessor in the informed consent procedures and at the time of each assessment. 

### 2.6. Assessment Schedule

Each participant would experience three assessments to go through the whole procedures in this study. The first assessment is for enrollment and would be given when women is confirmed eligible for participation. The second assessment would be conducted after 18th week postpartum but not later than 24th week. The final assessment would be performed in one year after delivery (Figure 1).

### 2.7. Interventions

All participants in EG and CG would be undergo postpartum pelvic floor evaluation according to standard comical procedures, which includes instructions for PFM strengthening with Kegel [12] and Knack [29] methods to improve voluntary contraction of the pelvic floor muscles, as well as daily living habits and posture education, such as reducing stool time, avoiding heavy lifting, etc. No extra intervention would be given to the participants in CG. 

In addition to the clinical standard pelvic floor evaluation, participants in EG would be provided with a Pelvic Floor Workout (PEFLOW). PEFLOW is a general program for physical training of the pelvic floor via entire body exercise. PEFLOW trains on coordination of breathing and muscle movement, maximum contraction of PFM, quick contraction of the PFM, and enduring contraction of PFM. The frequency of exercise following PEFLOW is 2 sessions a week for 12 weeks. It should be performed under the guidance of the professional physiotherapist for the whole process. It is designed for offline and online exercise. Due to COVID-19 pandemic prevention, PEFLOW in this study would be performed by the participants in EG at home under the online guidance of 2 physiotherapists. In order to keep the training effective, we would conduct the training in grouping [26] with each including less than 10 persons and ensure that no woman is over than 12 weeks postpartum at her first session of PEFLOW.

The Physiotherapist-online-guided PEFLOW (OG-PEFLOW) would be performed by participants in EG twice sessions a week for 12 weeks (Figure3). OG-PEFLOW would be provided via Zoom and in the form of live broadcasting. To monitor the performance of the participants, the participants would be requested to turn on the camera on their playing devices during the whole sessional procedures; however, they would be fully informed that no video or picture would be recorded or shot to protect their privacy. In each session of the OG-PEFLOW, a physiotherapist would perform exercise guidance, while another physiotherapist would monitor the performance of the participants and take notes. Details of the PEFLOW will be published in another manuscript. 

During the 12 weeks of intervention, participants in EG group would be requested to record their training load using RPE scale [30] every time after each training session. RPE quantitative evaluation of exercise load is calculated by “RPE score times x Exercise duration”. RPE scale indicates the exercise intensity in a specific time and the participants’ subjective psychological response to the stimulation from the exercise loads. In addition, Both EG and CG needs to record their training or exercise (if any) from the 6th week to 1 year postpartum. All of those records would be used for post-intervention assessment after 12-week intervention of EG.

The PEFLOW (Table 1 and Table 2) is a multimodal exercise program including moderate-intensity, aerobic, resistance, balance, and stretching exercise combined with PFMT, and the duration of each training session is about 60 min. Included in this program are ten sections, one for pelvic floor warm-up, eight for global exercises, and one for cooling down.

All participants in EG are informed to claim to the medical providers involved if any experiencing symptoms related to sport injury (e.g., knee pain, elbow pain, etc.). Any patients claiming to have such injury would be referred to the obstetric department or the physio therapist for treatment followed by an assessment for whether they should continue the training or not. An anticipated adverse event log would be prepared and sent to the principal investigator (PI) when such injury happens.

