### 4.1. Sample Analysis

Sample size was calculated according to the improvement rate of MOS grade after 12-week training using PASS 2019 software. According to the preliminary experiment, the improvement rate of MOS in the CG was 20% and that of women in EG was 60% at 6 months postpartum. Group sample sizes of 106 in each group achieve 90.248% power to detect a difference between the group proportions of 0.4. The CG proportion is 0.2. The EG proportion is assumed to be 0.4 under the null hypothesis and 0.6 under the alternative hypothesis. The test statistic used is the one-sided Z test (unpooled). However, in considering 20% of the possible dropout, a total of 260 women will be randomized.

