### 4.2. Statistical Analysis

Data will be analyzed using SPSS version 26.0 (SPSS, Inc., Chicago, IL, USA) and the statistically significant difference will be identified if *p* < 0.05. Descriptive statistics including numbers and proportions, means and standard deviations, or medians (P25, P75) will be used. Group differences in the primary and secondary outcomes will mainly use chi-square and student’s t tests. For primary outcome, we will count the rate of pelvic muscle strength reaching grade 4 at 6 months postpartum between EG and CG by chi-square test or Fisher’s exact test as appropriate. Analysis of the primary and secondary outcomes will be based on an intention-to-treat basis in consideration of the drop-offs from the follow-ups and be conducted by the statistician at Peking University Clinical Research Institute. For comparison between groups of quantitative data, the analysis of variance or Wilcoxon rank sum test will be used according to the data distribution; chi square test or exact probability method is used for counting data (if chi square test is not applicable), Wilcoxon rank sum test or CMH test is used for grade data, and logistic regression analysis is used for correlation analysis. Repeated ANOVA will be used to assess within-patient correlation. and multivariable linear regression models if potential confounders were imbalanced.

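### Women in the experimental arm train in small live online groups and controls are ungrouped, but the tests and the power calculation treat all women as independent

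*Protocol article*

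**What the plan says.** **Unit of randomisation.** Section 2.5 randomises individual women: "Eligible women would be randomized into two groups, the experimental group (EG) and the control group (CG), at a ratio of 1:1".

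**Delivery in EG.** Section 2.7 sets two sessions a week for 12 weeks, and "OG-PEFLOW would be provided via Zoom and in the form of live broadcasting". Women take part "at home under the online guidance of 2 physiotherapists", one leading the session and the other monitoring. On group size, "we would conduct the training in grouping [26] with each including less than 10 persons". The stated purpose of grouping is to keep the training effective.

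**Delivery in CG.** Both arms receive the standard pelvic floor evaluation with Kegel and Knack instruction and advice on habits and posture. Beyond that, "No extra intervention would be given to the participants in CG".

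**Analysis.** Section 4.2 states that "Group differences in the primary and secondary outcomes will mainly use chi-square"; it names t tests as well. The primary analysis is described there as follows: "count the rate of pelvic muscle strength reaching grade 4 at 6 months postpartum between EG and CG by chi-square test or Fisher’s exact test". The only correlation mentioned is within-patient, through repeated-measures ANOVA. Training group appears nowhere in the analysis.

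**Sample size.** Section 4.1 states that "Group sample sizes of 106 in each group achieve 90.248% power", using a one-sided unpooled Z test with CG at 0.2 and EG at 0.4 under the null and 0.6 under the alternative. It contains no design effect and no ICC.

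**The concern.** This is a partially nested design: women are randomised individually, but one arm is then treated in small groups. EG women in the same live session share its schedule, the correction given in it and any peer encouragement, so their outcomes may be more alike than those of women in different groups. CG women have no such link. Chi-square, Fisher's exact and t tests, and the Z-test formula in 4.1, all assume independence in both arms.

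With positive within-group correlation, the true variance of the EG rate exceeds the binomial variance those methods use. P-values would then be too small and the stated power too high. The article has chosen the primary test and the sample-size formula itself, so this concerns a stated choice and not merely a detail left to a later plan.

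**Working it through.** **Inputs from the article.** 106 women per arm for analysis; rates 0.2 (CG) and 0.6 (EG); null difference 0.4 − 0.2 = 0.2; 260 randomised, so 130 per arm; group size below 10, so at most 9.

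**Assumptions.** The ICC is not in the article; 0, 0.02, 0.05 and 0.10 are used. The 5% test is taken as two-sided, because 4.2 gives no sidedness. For group size *m*, 9 is the ceiling. A lower value allows for dropout: 130/9 = 14.4, so 15 groups, and 106/15 ≈ 7.07 women analysed per group.

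**Step 1: reproduce the plan's power.** Section 4.1 does not state alpha; a one-sided 0.025 fits.

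SE = √[(0.2×0.8 + 0.6×0.4)/106] = √(0.40/106) = 0.0614

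Power = Φ(0.2/0.0614 − 1.96) = 90.248%, the stated figure. A one-sided alpha of 0.05 would give 94.64%. The figure therefore assumes full independence.

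**Step 2: design effect, EG only.** DE = 1 + (*m* − 1)×ICC.

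**Step 3: actual level of the nominal 5% test of no average difference.** With equal rates and equal arms, the correct SE is √[(1 + DE)/2] times the naive one, so

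level = 2×{1 − Φ(1.96/√[(1 + DE)/2])}

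**Step 4: power for the 0.2-null test with the correct SE.**

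Power = Φ(0.2/√[(0.16 + 0.24×DE)/106] − 1.96)

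Example, *m* = 9 and ICC 0.05: DE = 1 + 8×0.05 = 1.40. The SE ratio in Step 3 is √1.20 = 1.095, giving a level of 7.4%. The SE in Step 4 is √(0.496/106) = 0.0684, giving power of 83.2%.

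| ICC (assumed) | DE, m = 7.07 / 9 | Actual level, m = 7.07 / 9 | Power, 0.2-null test, m = 7.07 / 9 |
|---|---|---|---|
| 0 | 1.00 / 1.00 | 5.0% / 5.0% | 90.2% / 90.2% |
| 0.02 | 1.12 / 1.16 | 5.7% / 5.9% | 88.2% / 87.5% |
| 0.05 | 1.30 / 1.40 | 6.8% / 7.4% | 85.0% / 83.2% |
| 0.10 | 1.61 / 1.80 | 8.6% / 9.8% | 79.6% / 76.3% |

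Smaller groups soften this: at *m* = 5 and ICC 0.05 the level is 6.2% and power 86.8%.

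**Step 5: simulation check.** Beta-binomial EG groups of 9 (100,000 runs, common rate 0.2 or 0.4) gave levels of 5.9–6.0%, 7.2–7.4% and 9.5–9.7% at ICC 0.02, 0.05 and 0.10, in line with Step 3.

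**Step 6: sample size for 90% power on the 0.2-null test.** n per arm = (0.16 + 0.24×DE)×(1.96 + 1.2816)²/0.2². With *m* = 9 this is 116, 131 and 156 at ICC 0.02, 0.05 and 0.10, against 106.

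**Step 7: plain test of no difference at 0.2 versus 0.6.** Replacing 0.2 by 0.4 in the numerator of Step 4, the worst case in the table (DE 1.80) gives Φ(0.4/0.0747 − 1.96), still above 99.9%.

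**The case against.** **The size is unknown and may be small.** This stands. The article gives no ICC, and women train at home on one standardised programme. The same two physiotherapists appear to serve all groups, and staff common to every group do not create differences between groups. Against this, the article itself expects grouping to help keep training effective, so an ICC of exactly zero should not simply be assumed.

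**Type I error is not inflated under every null.** This also stands. If the programme and its groups affect nobody, individual randomisation protects the level of the chi-square and Fisher tests. The inflated levels apply to the null of no average difference when real group effects exist and cancel out.

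**The power loss is not in the test that 4.2 names.** Largely correct. The loss applies to the 0.2-null test used for sizing in 4.1. Section 4.2 describes a comparison of the two arms, and at 20% versus 60% its power barely moves.

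**A group-aware model could be left to a fuller plan.** Only partly. Recording a group identifier may well be specified elsewhere, but the article names its primary test and power formula, and both ignore the groups.

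**Stronger readings the text does not support.** A reader might infer that the primary p-value is definitely too small, but that needs a positive ICC the article does not report. A reader might infer fixed group membership over all 24 sessions, but 2.7 gives only a size limit. A reader might call CG untreated, as the abstract's wording suggests, but 2.7 gives both arms Kegel and Knack instruction; what matters is that CG is ungrouped. A reader might say the primary confidence interval is too narrow, but none is planned, so this would apply only if an unadjusted interval were reported.

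**Conclusion.** The concern holds in conditional form. The EG arm is clustered by delivery, the CG arm is not, and neither the stated tests nor the power calculation allows for it. At an assumed ICC of 0.02 the effect is modest. At 0.05 to 0.10, with about 7 to 9 women per group, the nominal 5% test runs at about 7% to 10% and the power stated in 4.1 drops by about 5 to 14 percentage points. At 0.05 with groups of 9, the 131 analysable women per arm needed for 90% power already exceed the 130 randomised per arm.

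If the planned 20% versus 60% difference occurs, a test of no difference would almost certainly remain significant. The point matters for a smaller true effect, for the 0.2 null difference on which the trial was sized, and for the secondary outcomes. These figures rest on the assumed ICCs and group sizes and on normal approximations.

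**What to change.** 1. Record the training group of every EG woman, and any change of group. Without it the correction may be impossible later.
2. In 4.2, analyse the primary and secondary outcomes with a partially nested model (group effect in EG only) or with cluster-robust standard errors (EG groups as clusters, CG women as singletons). Use a small-sample correction, since there will be only about 15 groups. At the least, prespecify this as a sensitivity analysis beside the chi-square or Fisher test.
3. Report the estimated ICC.
4. In 4.1, say that 90.248% assumes no within-group correlation, and give power over an assumed ICC range such as the one above.

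The cost is one extra data field and a somewhat more complex model, with slightly wider intervals and a less favourable stated power.

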**Cooling Down**	Dynamic stretching, including upper and lower limbs, waist, back, and abdomen stretching and pelvic floor muscle relaxation with mini foam axis.			

**Table 2 ijerph-19-11073-t002:** Data collection and follow-up instruments.

		EG	CG	EG	CG	EG	CG
Baseline screen, Informed consent, Randomization							
The follow-up visits		The First		The Second		The Third	
Demographic data collection		◯	◯				
The MOS		●	●	●	●	●	●
POP-Q stage		●	●	●	●	●	●
Cough stress test		●	●	●	●	●	●
Vaginal relaxity		●	●	●	●	●	●
Pelvic floor electrophysiological test		◎	◎	◎	◎	◎	◎
Pelvic floor ultrasound		◎	◎	◎	◎	◎	◎
Spine X-ray		◎	◎	◎	◎	◎	◎
Body Composition		◎	◎	◎	◎	◎	◎
Hand grip test		◎	◎	◎	◎	◎	◎
Trunk endurance test		◎	◎	◎	◎	◎	◎
Questionnaires	PFDI-20	◯	◯	◯	◯	◯	◯
	PFIQ-7	◯	◯	◯	◯	◯	◯
	FSFI-6	◯	◯	◯	◯	◯	◯
	IPAQ-SF	◯	◯	◯	◯	◯	◯
	PSQI	◯	◯	◯	◯	◯	◯
Training record				✷	✷(if any)		
RPE				✷			
Adverse Event				☐	☐		

●: Data would be collected by pelvic floor professionals via vaginal palpation. ◎: Data would be collected by experienced General specialists as the examiners. ◯: data would be collected by requesting all participants to give answers through scanning a QR code. ✷: Recording by all the participants in EG only per their training record and RPE score given by themselves.: Optional items. Abbreviations: MOS: The modified Oxford Scale [3], which needs to be performed by inserting two fingers into the vagina for approximately 4 cm to feel the FPM contraction and give scale ranging from 0 (no contraction) to 5 (strong contraction).; POP-Q [5]: pelvic organ prolapse quantitation; PFDI-20: The Pelvic Floor Distress Inventory Questionnaire-20; PFIQ-7: Pelvic Floor Impact Questionnaire-7; FSFI-6: The 6-item Female Sexual Function Index; IPAQ-SF; International Physical Activity Questionnaire Score-Short Form; RPE: Ratings of Perceived Exertion.

**Table 3 ijerph-19-11073-t003:** Outline of Soring for general pelvic floor function.

Testing Items	Indicators	Compute Value	Score Value
POP-Q	Stage 0	0	
	Stage I	1	
	Stage II	2	
	Stage III	3	
	Stage IV	4	
Cough stress test	Yes	1	
	No	0	
Vaginal relaxation	≥4 fingers	4	
	>3 fingers, and <4 fingers	3	
	=3 fingers	2	
	>2 fingers, and <3 fingers	1	
	≤2 fingers	0	
Pelvic floor electrophysiological test [40]	<20 cm^2^Hg	1	
	≥20 cm^2^Hg	0	
			* Total Score ^1^
PFDI-20	-	Comprehensive score	
PFIQ-7	-	Comprehensive score	
FSFI-6	-	Comprehensive score	
			* Total Score ^2^

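### Adverse events are ascertained unequally: only the exercise arm is told to report, and only sport injury, while Table 2 lists an apparently optional item for both arms with no 1-year entry

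*Protocol article*

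**What the plan says.** Section 2.7 (Interventions) gives the only reporting instruction: "All participants in EG are informed to claim to the medical providers involved if any experiencing symptoms related to sport injury". The examples there are knee and elbow pain. Such women are referred and assessed for continuation, and "An anticipated adverse event log would be prepared and sent to the principal investigator (PI) when such injury happens". No corresponding sentence addresses CG.

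Table 2 has an "Adverse Event" row. It shows an open box for EG and for CG under the second visit, and nothing under the first or third. The legend defines the four other symbols. Its last entry reads "RPE score given by themselves.: Optional items", with no symbol in front of the colon in the text available for this review.

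On timing, section 2.6 says "The second assessment would be conducted after 18th week postpartum but not later than 24th week", and "The final assessment would be performed in one year after delivery".

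On contact, section 2.7 says "The frequency of exercise following PEFLOW is 2 sessions a week for 12 weeks". EG sessions are live and on camera, and a second physiotherapist watches and takes notes. CG receives the standard postpartum evaluation and advice and nothing further. Both arms are asked to keep an exercise record up to one year.

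**The concern.** A comparison of harms needs the same question, asked in the same way over the same period, in both arms. Here one arm is prompted and observed, and the other has only a table entry that may be optional. The trial is open-label for participants and physiotherapists and starts 6 to 12 weeks after delivery. It excludes women at POP-Q stage III or above but not those at lower stages. The Discussion presents exertion scoring as a safeguard for safe training, and the Conclusions look ahead to clinical promotion of the programme. A statement on safety relative to control will be wanted, and the reporting rules as fixed would not support one.

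There is also a gap in scope. The instruction and the log are tied to sport-type injury. Any other event, such as a new pelvic floor complaint, has no stated route except the Table 2 row.

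**Working it through.** The plan gives no figure for adverse events, so there is none to reproduce. The check sets the provisions side by side and then illustrates the direction and size of the distortion.

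**1. Who, what and when**

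| | EG | CG | Source |
|---|---|---|---|
| Told to report | Yes, sport-injury symptoms | Not stated | Section 2.7 |
| Event-driven log | Yes | Not stated | Section 2.7 |
| Monitored contacts during the programme | 2 × 12 = 24 | None comparable | Section 2.7 |
| Table 2 entry, second visit | Open box | Open box | Table 2 |
| Table 2 entry, 1-year visit | Blank | Blank | Table 2 |

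**2. Is the row optional?** Every other Table 2 symbol has its own legend entry. The open box is the only symbol without one, and the entry for optional items is the only one without a symbol. By elimination the two belong together. This is an inference, because the symbol was lost when the text was read from PDF. A reader with the published table can settle it.

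**3. Illustration.** The inputs are 260 women randomized 1:1 (sections 2.5 and 4.1), so 130 per arm, plus two assumptions that the article does not give: a true event risk r, equal in both arms, and the share of events captured, c_EG and c_CG.

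- Recorded events per arm = 130 × r × c
- Recorded risk ratio = c_EG / c_CG when the true ratio is 1, whatever the value of r
- Spurious risk difference = r × (c_EG − c_CG)

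With r = 10%:

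| c_EG | c_CG | EG events | CG events | Risk ratio | Spurious difference |
|---|---|---|---|---|---|
| 90% | 90% | 11.7 | 11.7 | 1.0 | 0 points |
| 90% | 50% | 11.7 | 6.5 | 1.8 | 4 points |
| 90% | 30% | 11.7 | 3.9 | 3.0 | 6 points |
| 50% | 50% | 6.5 | 6.5 | 1.0 | 0 points |

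With r = 5% the two spurious differences halve to 2 and 3 points. With r = 20% they double to 8 and 12 points. The risk ratios stay at 1.8 and 3.0. The last row shows that capture which is low but equal lowers the counts without distorting the ratio. The comparison is damaged by unequal capture.

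**The case against.** The best defence is that the sentence in section 2.7 is a safety instruction to women who are exercising. It naturally addresses EG, and it does not say that CG events go uncollected. Table 2 includes CG, with the same symbol. The article condenses a fuller protocol that may say how events are elicited. Safety is not a listed outcome in section 4, and section 4.2 plans no between-arm test of adverse events. All of this is fair and limits the point. It does not remove it: the article does fix a reporting instruction, fixes it for one arm and one type of event, and leaves it unreconciled with its own table.

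Three stronger readings are tempting, and the documents do not support them.

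- *Harms of PEFLOW will be under-recorded.* This is not established. EG has the instruction, the event-driven log and 24 observed sessions, so the expected bias is relative under-recording in CG. Under-recording in EG is possible, because the item may be optional and the instruction covers only sport injury, but it is not certain.
- *Adverse events are collected only at visit 2.* The second-visit column cannot mean that. The exertion score and training record also appear only there, yet section 2.7 has the score recorded after every session and exercise recorded to one year. The log is triggered by the event. The second visit also follows the 12-week programme. The gap that the article leaves is from visit 2 to one year, plus the absence of any stated prompt in CG throughout.
- *The row is optional as a matter of fact.* It is the most plausible reading of a damaged legend. The box might also mean that the item is completed only if an event occurred. The point stands without it, on the EG-only instruction and the empty third visit.

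**Conclusion.** The point holds in a limited form. As written, harms are ascertained unequally: actively in EG and for sport injury only, and in CG only through an apparently optional table entry. Neither arm has an entry at one year. Recorded events would tend to look relatively higher under PEFLOW with no true difference. Under the assumed capture rates the recorded risk ratio is 1.8 to 3.0; the event risk and capture rates are illustrative and do not come from the article. Events other than sport injury may be missed in either arm.

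The primary outcome, pelvic floor muscle strength, is not affected. The incidence of injury in EG could still be described. A comparative safety statement could not be supported. A reader might go on to calculate how often a significance test would show a false difference, but no such test is planned, so that would describe an analysis outside the plan.

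**What to change.** Reconcile section 2.7 with Table 2:

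- Make adverse-event collection mandatory in both arms, and mark it so in Table 2 under the second and third visits with a defined symbol.
- Put the same question to EG and CG, covering the same recall period and any adverse event, not sport injury alone. One added item in the WeChat form that section 3 already uses at every visit would do.
- Report these events by arm.
- List EG session-level injury reports separately and keep them out of the between-arm comparison.

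The cost is one questionnaire item at two existing visits, an edit to Table 2 and a little more data handling. The referral and continuation procedure for injured women need not change.
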